## Abstract

**Background:**

The gliding surface of total knee endoprostheses is exposed to high loads due to patient weight and activity. These implant components are typically manufactured from ultra-high molecular weight polyethylene (UHMWPE). Crosslinking of UHMWPE by ionizing radiation results in higher wear resistance but induces the formation of free radicals which impair mechanical properties after contact with oxygen. Medium-crosslinked UHMWPE enriched with vitamin E (MXE) provides a balance between the parameters for a sustainable gliding surface, i.e., mechanical strength, wear resistance, particle size, and oxidation stability. Therefore, a gliding surface for knee endoprostheses made up from this material was developed, certified, and launched. The aim of this study is to compare this new gliding surface to the established predecessor in a non-inferiority design.

**Methods:**

This multicenter, binational randomized controlled trial will enroll patients with knee osteoarthritis eligible for knee arthroplasty with the index device. Patients will be treated with a knee endoprosthesis with either MXE or a standard gliding surface. Patients will be blinded regarding their treatment. After implantation of the devices, patients will be followed up for 10 years. Besides clinical and patient-related outcomes, radiological data will be collected. In case of revision, the gliding surface will be analyzed biomechanically and regarding the oxidative profile.

**Discussion:**

The comparison between MXE and the standard gliding surface in this study will provide clinical data to confirm preceding biomechanical results in vivo. It is assumed that material-related differences will be identified, i.e., that the new material will be less sensitive to wear and creep. This may become obvious in biomechanical analyses of retrieved implants from revised patients and in radiologic analyses.

**Trial registration:**

ClinicalTrials.gov, NCT04618016. Registered 27 October 2020, https://clinicaltrials.gov/study/NCT04618016?term=vikep&checkSpell=false&rank=1.

All items from the World Health Organization Trial Registration Data Set can be found in Additional file 1.

**Supplementary Information:**

The online version contains supplementary material available at 10.1186/s13063-023-07811-1.

## Background

Total knee arthroplasty (TKA) is the only effective treatment for end-stage symptomatic knee damage caused by osteoarthritis or rheumatic arthritis. There is a trend towards younger and more active patients who receive a TKA, making higher demands towards their implant. Furthermore, a considerable share of (younger) TKA patients is overweight or obese [1, 2]. Higher activity levels and higher patient weight induce higher loads on the prosthesis components, especially on the meniscal component, which serves as gliding surface for articulation of the femoral component. Increased loads on the gliding surface may result in wear of the device material, leading to debris and aseptic loosening [3, 4]. This emphasizes the importance of the material properties on the outcome of TKA. After its introduction in the early 1960s, ultra-high molecular-weight polyethylene (UHMWPE) has represented the material of choice for the gliding surface [3]. Research on UHMWPE aimed to improve material properties and wear resistance. Improvements regarding wear resistance were achieved by crosslinking of UHMWPE through ionizing radiation. However, this process induces formation of free radicals in the material, which after contact with oxygen leads to oxidative degeneration, material embrittlement, and impairment of mechanical properties [5]. Remelting and annealing were introduced as post-irradiation treatments to improve oxidative stability of the material, but negative effects were induced by these treatments regarding mechanical properties [6]. Therefore, a method to prevent oxidation of crosslinked UHMWPE without modifying mechanical properties was searched for.

Vitamin E is an effective natural antioxidant, occurring in cell membranes and preventing phospholipids from being oxidized by free radicals [7]. Similarly, vitamin E prevents UHMWPE from irradiation-induced oxidation [8] and therefore represents a promising stabilizer of crosslinked UHMWPE. Two methods are deployed for supplementation of UHMWPE with vitamin E: blending, where the raw material is mixed with vitamin E powder before the irradiation and cross-linking process; and doping, where the irradiated implant is doped with vitamin E. Biomechanical data indicated that vitamin E-enriched crosslinked UHMWPE has an advantageous oxidation profile (also after aging) while maintaining mechanical properties important for the gliding surface of a TKA [9, 10, 8, 11].

In contrast to the application of highly crosslinked vitamin E-enriched UHMWPE for the liners in hip arthroplasty, where a large amount of clinical data is available [12–17], such data for TKA is rather rare. Flament et al. were the first to publish clinical results on vitamin E polyethylene bearings in TKA, providing good results for the device [18]. Takemura et al. compared clinical results of gliding surfaces made from highly crosslinked UHMWPE with and without vitamin E 2 years postoperatively, detecting no significant differences between both groups regarding alignment, Knee Society Score (KSS), complications, and radiolucent lines [19]. Likewise, Ftaita et al. compared clinical results of gliding surfaces made from conventional UHMWPE and highly crosslinked vitamin E-enriched UHMWPE, without any significant differences for complications, radiological results, forgotten joint score, and knee injury and osteoarthritis outcome score [20]. Using the same implants as in the studies discussed before, Orita et al. showed that highly crosslinked vitamin E-enriched UHMWPE gliding surfaces produced more, smaller and rounder wear particles compared to conventional UHMWPE, isolated from TKA patients’ synovial fluid [21]. Spece et al. performed a retrieval analysis of gliding surfaces made from highly crosslinked UHMWPE with and without vitamin E after rather short implantation times (mean 1.2–1.5 years) [22]. In the former group, the most prevalent reason for revision was instability (28.2%), followed by infection (23.3%) and aseptic loosening (17.5%), whereas in the group without vitamin E, infection (32.8%) was the most prevalent reason for revision, followed by aseptic loosening (25.4%) and instability (19.4%). Oxidation index was significantly increased in some areas of the retrievals without vitamin E and so were the articulating surface damage scores for burnishing, scratching, and pitting [22].

After extensive research in material science and biotribology a medium crosslinked, vitamin E-enriched gliding surface (MXE) was developed and launched in 2020. This material provides a balance between the parameters for a sustainable gliding surface, i.e., mechanical strength, wear resistance, particle size, and oxidation stability.

The aim of this study is the comparison of clinical outcome, oxidation profile, and wear analysis of MXE and the predecessor, ß-sterilized UHMWPE (ß-PE) for TKA. In this randomized controlled single blind clinical trial, it shall be shown that the new material is at least as efficient as the predecessor (non-inferiority).

## Methods/design

### Eligibility criteria and recruitment

Identification of eligible participants is performed by the investigators (surgeons) of the participating study centers from the general patients visiting their clinic for treatment of the indications mentioned. All patients designated for TKA with an e.motion UC Pro or e.motion PS Pro endoprosthesis (criteria see below) at the participating study centers will be screened for inclusion. The study proposal, including nature, purpose, and risks of the study, will be explained to the patient by the investigator during the preliminary consultation. A patient information sheet in layperson-comprehensible language is provided to the patient. The patient will be given sufficient time to consider the implications of the study before deciding whether to participate. Patients participating in the study must understand and agree with the patient information and be willing and able to participate in the study, including long-term follow-up visits. The written consent form will be obtained by one of the investigators of the study center.

There are no specific strategies for the identification of participants like advertisements or similar activities. Also, no coordinators are employed to identify eligible patients.

Eight centers in Germany and France are participating in the study, thereof are 3 academic hospitals (a list of the participating study centers is provided in Additional file 1). Study centers were accepted for study participation only after a successful site selection visit by the sponsor, where knowledge of and experience with the study devices was proven and ability to perform the study according to GCP principles was demonstrated.

The risk of not reaching the recruitment target is minimized by the inclusion of study centers which confirmed to be able to enroll 80 study patients during the recruitment phase of 18 months. By including several study centers, the risk of not reaching the recruitment target is minimized as the study protocol allows enrollment of up to 120 patients per study center in case that another study center will not reach the scheduled number of patients to be enrolled. To avoid center effects, the maximum number of patients to be enrolled by one study center is 120.

According to the instructions for use of the manufacturer, indications for an e.motion UC Pro and e.motion PS Pro endoprosthesis are as follows:

Severe knee joint disorders that cannot be treated through other therapies.Degenerative gonarthrosisRheumatoid arthritisPosttraumatic arthrosisSymptomatic knee instabilityKnee stiffnessKnee joint deformity

According to the instructions for use of the manufacturer, e.motion UC Pro and e.motion PS Pro endoprosthesis is contraindicated:In patients for whom reconstructive surgery to treat the joint disorder is an optionIn case of acute or chronic infections near the joint (systemic infections)In case of secondary diseases influencing the function of the joint implantIn case of severe osteoporosis or osteomalacia with cementless implantsIn case of bone tumors in the region of implant fixationIn case of poor bone quality and osseous malformations, diseases in the area of the implant fixation, which may primarily or subsequently affect the stability of the joint replacement anchorageIn case of known hypersensitivity to the implant materialsIn all of the areas of application not listed under Indications

According to the study protocol, further exclusion criteria for the study are as follows:Age below 18 years or over 80 yearsAmerican Society of Anesthesiologists (ASA) class ≥ 3Pregnancy

### Sample size

The aim of the present study is to show the non-inferiority of the MXE bearing material compared to the β-PE in terms of clinical and functional outcome, which is measured by the KSS. Lizaur-Utrilla et al. showed in their study that the minimally clinically important difference is at least 9 points for the KSS knee (kKSS) and at least 10 points for the KSS function (fKSS) [23]. In order to show non-inferiority of the new material, 10 points were selected as non-inferiority margin for sample size calculation. A recent publication showed that KSS results 5 years after primary TKA vary with a standard deviation of 30 points [24]. Thus, 30 points was used as standard deviation for sample size calculation.

Therefore, a two-sample *t* test with *α* = 0.05 and 80% power and a non-inferiority design (MXE vs. β-PE) with a non-inferiority margin of 10 points requires 224 patients in total (112 patients per group). Assuming a drop-out rate of 20% due to the long-term follow-up, in total 280 patients are necessary to meet the power criteria for the primary endpoint.

As the study includes two variations of the investigational device (e.motion UC Pro and e.motion PS Pro) together with the different bearing materials, in total, 560 patients will be randomized into this study. To avoid center effects, a maximum of 120 patients may be recruited per center. During study preparation, only centers were considered, which are able to recruit a sufficient number of patients according to their throughput of patients.

Patients who withdraw their consent for study participation will not be replaced by new patients. Intraoperative drop-outs due to deviation from the randomization protocol will be replaced by new patients.

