### Randomization and blinding

For each participating center a separate randomization list be will prepared by the sponsor to avoid center specific effects and to assure a balanced (1:1) distribution of both treatments within one center (stratification). Randomization lists will be computer-generated using random block lengths.

Randomization is taking place after the patient consented to be part of the clinical investigation (see Fig. 1). Intraoperatively, the sealed opaque envelope containing the information to use either the MXE or the β-PE gliding surface will be opened to randomly allocate the procedure for the specific type of bearing material and to ensure allocation concealment. Whether the study site is using the e.motion PS Pro or the e.motion UC Pro implant is independent from the randomization and according to the standard treatment of each site.

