**Fig. 1 Fig1:**
[figure not shown]
Patient inclusion flowchart

While study patients will be blinded, blinding of the surgeon is not possible due to the different color of the implants. Due to the infrastructure and capacity reasons in (some of) the participating study centers, the KSS is recorded by the investigators/surgeons, who typically performed the implantation of the devices. Therefore, blinding of outcome assessors cannot be ensured. The analyzation of radiological results will be performed in a blinded manner.

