### Intervention

The implants are CE certified, and the TKA is performed according to the instructions for use. It will be further documented if patella resurfacing is performed, if the image-free navigation system OrthoPilot (Aesculap AG, Tuttlingen) is used, and if implants with or without the advanced surface technology (AS) are used.

In case of an intraoperative finding that the endoprosthesis is not indicated for a specific patient, the patients will be excluded from the study. Surgeries will be performed or, in cases of training procedures, supervised by board certified orthopedic surgeons. All centers meet the certification standards such as the German EndoCert system. Preoperative measures include digital planning of the prosthesis and standardized imaging, antiseptic, and anticoagulation standards. Furthermore, surgical approaches, anesthesia, and tourniquet use are performed according to the standards of each center. Postoperative regimen is not stipulated by the study plan to allow the study centers to follow their standard treatment regimen. It is expected that there are no major differences between the study centers regarding postoperative regimen. There may be minor differences between study centers, but as each study center includes patients in both study groups, the potential for cointervention bias is expected to be small.

Postoperative treatments including standardized weight bearing, physical therapy, anti-thrombotic medication, pain management, and discharge to rehabilitation centers accord to the standard proceeding in each study center. No difference is made between patients of the study groups or other patients not participating in the study.

No restrictions to any concomitant therapy or intervention are defined in this study. No additional surgical or interventional procedure is related to the study.

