**Table 1 Tab1:**
[figure not shown]
Data acquisition during the course of the study

^*^Required images: knee AP (standing), knee lateral (standing)

^**^Additionally: long leg (standing)

(X): radiographic evaluation may be performed at either visit

There are no specific plans to promote participant retention and complete follow-up. The patients are informed about the follow-up visits before their decision to participate in the study. The visits are kept to a minimum (3 months, 12 months, 5 years, 10 years) and accord to typical follow-up examinations also performed in non-study patients. In addition, patients will receive the OKS self-assessment score at 3 and 7 years postoperatively, to reduce loss-to follow-up rate and allow better monitoring of study patients. Patients will be requested to send the OKS questionnaire back to the study center.

Reasonable effort should be made by the study centers to contact any patient lost to follow-up during the course of the study in order to complete assessments and retrieve any outstanding data and study supplies.

The final programming will be performed after closure of the database by use of an appropriate statistical software package SAS. The sponsor has an overview of results from all participating centers. All data will be analyzed by means of appropriate tables, figures, listings, and statistical tests. Missing data will be analyzed as such and will not be replaced by estimates. The statistical analysis of the primary endpoint has a confirmative character, whereas the secondary endpoints will be analyzed explorative. This must be considered when interpreting the *p*-values and confidence intervals. The description of the patient cohort in means of demographic data and the baseline values of investigated parameters will take place as whole as well as grouped by the therapy group. Analyses will be performed according to the intent-to-treat principle. The consistency of the results will be tested by per-protocol analysis (sensitivity analysis).

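### Patients whose allocation is not followed in theatre are called drop-outs and replaced, which conflicts with the stated intent-to-treat analysis and with the count of 560 randomised

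*Protocol article*

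**What the plan says.** All references are to the protocol article.

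- **Sample size:** "Intraoperative drop-outs due to deviation from the randomization protocol will be replaced by new patients". The sentence before it sets the opposite rule for another group: "Patients who withdraw their consent for study participation will not be replaced by new patients". The section plans 560 randomised patients in total.
- **Randomization and blinding:** "Randomization is taking place after the patient consented to be part of the clinical investigation". The arm is revealed later, in theatre: "Intraoperatively, the sealed opaque envelope containing the information to use either the MXE or the" β-PE surface is opened. On blinding, "blinding of the surgeon is not possible due to the different color of the implants". The surgeon who implanted the device typically also records the Knee Society Score (KSS), the primary outcome: "Therefore, blinding of outcome assessors cannot be ensured".
- **Intervention:** "In case of an intraoperative finding that the endoprosthesis is not indicated for a specific patient, the patients will be excluded from the study". The text does not say whether this is settled before or after the envelope is opened.
- **Data collection, management, statistical analysis and monitoring:** "Analyses will be performed according to the intent-to-treat principle". A per-protocol analysis serves as the sensitivity analysis, and missing values are not imputed.

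**The concern.** Intent-to-treat keeps every allocated patient in the allocated arm whatever was implanted. The replacement rule applies to patients who already have an allocation, and it treats them as having left the trial. If they are not followed they have no 10-year KSS, and without imputation they cannot enter the primary t test. The analysed set would then be allocated patients minus those whose allocation was not followed.

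The person able to depart from the allocation knows the arm at that moment. Any tendency to depart more often in one arm, in patients with a worse prognosis, would carry into the comparison. Because the places are refilled, the final numbers would look complete and would not reveal the loss. In a non-inferiority trial, losing poorer performers from the MXE arm works in favour of the claim.

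**Working it through.** **1. Do the passages conflict?** A departure from the randomisation protocol during surgery needs a known allocation, and the envelope opened in theatre is what discloses it. On the natural reading, the patients in the replacement rule have been allocated. The article labels them drop-outs and nowhere says that they are followed or analysed as allocated. The analysis section promises intent-to-treat. As written, the two do not fit together. The contrast with consent withdrawals, which are not replaced, shows that this group is handled differently on purpose.

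**2. The plan's own sample size.** Inputs from Sample size: margin 10, SD 30, alpha 0.05, power 80%, drop-out 20%. Sidedness is not stated.

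- n per group = 2 × (1.645 + 0.842)² × 30² / 10² ≈ 111.3, so 112, or 224 in total. The t-test power at 112 per group is 0.800.
- 224 / 0.80 = 280; 280 × 2 implant variants = 560.

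The figures reproduce with a one-sided alpha of 0.05 (one-sided 0.025 would give 142 per group). This point disputes none of them.

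**3. Effect on the count randomised.** If a share p of randomised patients is replaced until 560 remain, the number randomised is 560 / (1 − p). The article gives no p. As an assumption, p = 2% gives 560 / 0.98 = 571.4, so 572; p = 5% gives 560 / 0.95 = 589.5, so 590. Any p above zero contradicts 560 as the number randomised.

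**4. Possible bias (assumed values throughout).** Let p be the share of the MXE arm lost selectively, with no such loss in the other arm. Let g be how many KSS points lower those patients would have scored than the patients analysed. Then:

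- bias = p × g, in favour of MXE;
- SE = 30 × √(2/112) = 4.01 for one implant variant at the planned 112 per arm;
- one-sided type I error = 1 − Φ(1.645 − bias / SE), against a nominal 0.05.

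| p | g (points) | Bias (points) | Share of 10-point margin | Type I error |
|---|---|---|---|---|
| 2% | 15 | 0.30 | 3% | 0.0582 |
| 2% | 30 | 0.60 | 6% | 0.0674 |
| 5% | 15 | 0.75 | 7.5% | 0.0725 |
| 5% | 30 | 1.50 | 15% | 0.1019 |

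If the loss is equal in both arms and unrelated to prognosis, the bias is zero. In patient numbers, 2-5% of the roughly 140 per arm planned for one variant is about 3 to 7 patients.

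**5. Power if these patients are kept but not replaced.** In the worst case they yield no KSS on top of the 20% drop-out. Then 280 × 0.98 × 0.8 = 219.5 patients are evaluable at 2%, and 280 × 0.95 × 0.8 = 212.8 at 5%. Power is 0.795 and 0.784.

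**The case against.** The replacement sentence stands in the Sample size section and governs recruitment. Replacing a patient does not by itself remove that patient from the analysis. The one sentence that governs the analysis says intent-to-treat, and detailed definitions of analysis sets commonly sit in the full protocol or analysis plan, which are not shown. This stands in part: replacement and intent-to-treat can coexist. It does not remove the conflict, because the article calls these patients drop-outs, and a dropped patient cannot contribute to an unimputed 10-year t test.

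A reader might also infer more than the documents support:

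- **That surgeons are shaping the groups.** The two gliding surfaces are said to differ only in material. The article gives no reason to abandon one of them in difficult knees, and no deviation rate. There is opportunity, not evidence.
- **That the exclusion for an implant found not to be indicated is related to arm.** It concerns the implant system used in both arms and has no evident link to allocation. The order of steps is not given in the text, and the inclusion flowchart is not available here. Before opening, such an exclusion is harmless; the wording merely fails to confine it to that point.
- **That the per-protocol set would be almost the same as the intent-to-treat set.** Its definition is not shown, and other deviations over 10 years could still separate the two.

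**Conclusion.** The conflict is real and does not depend on any assumed rate: post-allocation patients are labelled drop-outs and replaced, while the analysis is declared intent-to-treat and 560 is given as the number randomised. The size of any resulting bias cannot be derived from the documents. Under the assumption of one-sided, prognosis-related loss of 2-5% of an arm with a gap of 15-30 points, the shift is 0.3-1.5 points (3-15% of the margin), and one-sided type I error rises from 0.05 to between about 0.06 and 0.10. Under equal, non-selective loss it is nil. The article does not show that the trial's intent-to-treat analysis will in fact be broken or that its result is biased. It leaves a rule that would permit this and should be closed before the primary analysis.

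**What to change.** State the following by short amendment or in the analysis plan:

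1. Drop-out and exclusion in theatre, including for an endoprosthesis found not to be indicated, apply only to patients whose envelope has not been opened. These patients may be replaced.
2. Every patient whose envelope was opened stays in follow-up, subject to consent, and in the intent-to-treat set under the allocated arm, whatever surface was implanted. Allocation deviations are handled only in the per-protocol set.
3. Patients already replaced are restored to the intent-to-treat set where data and consent allow. Counts and reasons are reported by arm, with the actual number randomised.

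The replacement sentence need not be deleted: additional recruits may be kept, provided the patients they replaced also stay in the intent-to-treat set. Nor does curing this conflict require a new rule that both analyses must agree. The surgeon's choice of implant in theatre is untouched; only the patient's status in the trial and the analysis changes.

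The cost is follow-up of the affected patients, whose number is not stated, and a small loss of precision. If none were replaced and none gave a KSS, power would be 0.795 to 0.784 at the assumed 2-5%. The article reports 435 patients included by May 2023 and expects the last patient out in Q4 2033, so there is time to act, although recovery of early cases depends on their consent and on what data were kept.
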